### Data collection

2.5

Data will be collected in case records form (Supplementary materials 2). Data will be transferred to electronic records and stored in the secure computers of Hamad Medical Corporation. The access log to these computers will be restricted to the primary investigator. Case record forms will be kept at safety cabinets in HMC. When there is a need for data alteration in the case record form, this will involve striking through the data with a straight line and countersigned by the investigator involved. Patients have been educated that they can withdraw from the study at any time, and when such a decision is made, patient's records (both papers and electronics) will be removed as well as blood samples and destroyed in keeping with regulatory requirements. Additionally, the parent medical teams will be notified.

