### Interventions

2.4

Once allocated to one of the two study arms, the study participants will be administered the study medication as either enteric-coated or plain Aspirin on day 1. Patients assigned will be prescribed plain loading dose (Dispersible 300 mg stat followed by Aspirin 75 mg tablets, Actavis UK Ltd) or EC Aspirin loading dose (300 mg stat followed by100 mg, Bayer, Germany) for 3 days (study duration). Irrespective of the design of the study, all patients enrolled in the study will receive other standards of care management according to HMC ischemic stroke guidelines. Patients will be required to give blood samples (10 mL) for estimation of the TXB2 level at baseline and on day 3, which marks the end of the study. Blood samples will be taken as part of the patient's routine investigation/care by the phlebotomist. Study samples will be taken by a designated study investigator as per standard protocols consistent with HMC guidelines. Study samples will be kept in labeled with anonymous patient-specific identifiers and kept in study refrigerators until completely used. Patients will be kept on other treatments constituting the usual standards of care management for established ischemic stroke, and this will be maintained throughout the study. We anticipate that it would take about one month to complete patient recruitment. Following the end of the study, laboratory analysis of biological samples will be carried out within 3 weeks with subsequent data evaluation and analysis.

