### Primary outcomes

2.6

Incidence of Aspirin non-responders at day 3 (level of residual serum TXB2 associated with elevated thrombotic risk (<99.0% inhibition or TXB2 >3.1 ng/mL).

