### Secondary outcomes

2.7

Incidence of Gastrointestinal bleeding consequent upon aspirin therapy (major and minor bleeding).

Gastrointestinal bleeding is classified as major bleeding: 2 g loss of hemoglobin or requirement of hospitalization; Minor bleeding: any bleeding less severe than above.^[22]^

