#### Analysis set

2.8.2

The full analysis Set utilizing Intention to treat methodology will be used for the primary efficacy analysis. Per-protocol set analysis will be attempted for the primary efficacy outcomes.

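### Destroying the records and samples of every patient who withdraws conflicts with the planned intention-to-treat set and can remove bleeds from the trial's count

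*Protocol article*

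**What the plan says.** Four places in the protocol article bear on this.

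- **2.5 Data collection.** Patients are told that "they can withdraw from the study at any time". When one does, that patient's paper and electronic records "will be removed as well as blood samples and destroyed in keeping with regulatory requirements". The parent medical team is notified. Nothing is exempted: not data gathered before withdrawal, not the allocated arm, not adverse events.
- **2.8.2 Analysis set.** "The full analysis Set utilizing Intention to treat methodology will be used for the primary efficacy analysis". A second analysis is planned: "Per-protocol set analysis will be attempted for the primary efficacy outcomes".
- **2.6 and 2.7 Outcomes.** The primary outcome is "Incidence of Aspirin non-responders at day 3", judged from serum TXB2. The secondary outcome is "Incidence of Gastrointestinal bleeding consequent upon aspirin therapy (major and minor bleeding").
- **2.4 Interventions.** Blood is drawn "for estimation of the TXB2 level at baseline and on day 3, which marks the end of the study". Laboratory work follows the end of the study and is to be done within three weeks.

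**The concern.** An intention-to-treat set keeps every allocated patient in the allocated arm, including those who leave. Section 2.5 removes those who leave from the study file altogether. They could not be analysed, counted by arm in a disposition table, or entered as missing in a sensitivity analysis. This is not a detail that an analysis plan could supply later, because no analysis plan can restore destroyed records.

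The design adds to the worry. The trial is open-label and patients are allocated by admission order, so a decision to leave may depend on the arm or on tolerability. Blinding the outcome assessors and analysts (2.3) does not prevent that. A gastrointestinal bleed is a plausible reason to leave, and it is also the event that the secondary outcome counts. Section 2.9 passes serious adverse events to the treating team but does not say that the trial keeps them. At stake is an exclusion that may be selective and that leaves no trace in the trial's own data.

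**Working it through.** The check is mainly one of logic. Arithmetic serves only to show scale.

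**Step 1. What each type of patient leaves behind under 2.5**

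| Patient | Records under 2.5 | Can 2.8.2 and 2.7 be followed? |
|---|---|---|
| Stops study drug, stays in study | Kept (2.5 does not mention this case) | Yes |
| Stays in study, day-3 sample missed | Kept | Yes, as a missing outcome |
| Withdraws from study before day-3 draw | Destroyed | No. There would be no day-3 TXB2 under any policy, but the arm, the baseline value and any bleed are lost too |
| Withdraws after day-3 draw, before assay | Destroyed, with the sample | No. An obtainable primary outcome is lost |

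The last row is possible because of the timing in 2.4. The day-3 draw ends the patient's participation, but the assay comes later.

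**Step 2. Scale**

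Inputs: N = 42 (2.2) and 21 per arm (2.8.1). The article states no withdrawal or bleeding rate, so the counts below are assumptions.

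- Share of an arm per erased patient: 1/21 = 4.8%.
- Observed bleeding rate after erasure = (bleeds − erased bleeds) / (21 − erased patients):
  - 1 bleed, 1 erased: 1/21 = 4.8% becomes 0/20 = 0%.
  - 2 bleeds, 1 erased: 2/21 = 9.5% becomes 1/20 = 5.0%.
  - 3 bleeds, 2 erased: 3/21 = 14.3% becomes 1/19 = 5.3%.

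**Step 3. How far the primary comparison could move**

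Take assumed non-response counts of 10/21 (enteric-coated, EC) and 3/21 (plain), and apply Fisher's exact test, two-sided:

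| Patients erased | EC v plain | p |
|---|---|---|
| None | 10/21 v 3/21 | 0.043 |
| 1 EC non-responder | 9/20 v 3/21 | 0.043 |
| 2 EC non-responders | 8/19 v 3/21 | 0.078 |
| 2 plain responders | 10/21 v 3/19 | 0.046 |
| 2 EC responders | 10/19 v 3/21 | 0.017 |

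The result moves either way or not at all, depending on who is erased. In each row the erased patients have left after the day-3 draw, since anyone leaving before it has no outcome to erase.

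**Step 4. Power**

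Section 2.8.1 claims about 80% power at 21 per arm for a 50% difference in means, two-sided alpha 0.05. It gives no standard deviation, so that figure cannot be reproduced from the article. Solving backwards with a t-test gives a standardised difference of 0.886. Holding that fixed, power is 75.7% at 19 per arm, 70.7% at 17 per arm, and 77.8% at 19 v 21. Withdrawals before the day-3 draw cost this power whether or not records are destroyed, and the calculation is for a mean while the primary outcome is binary. These figures therefore do not measure the harm done by the destruction rule.

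**The case against.** The strongest reply is that the rule may never bite. Treatment lasts three days in patients recruited from a stroke unit, and if nobody withdraws from the study the two sections do not collide. That stands as a limit on size. It does not remove the conflict, since a withdrawal rule has to work when someone withdraws.

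A reader might infer that intention to treat is impossible and that the full analysis set shrinks to completers. The text does not support this. Only withdrawal from the study triggers destruction. Patients who stop drug, deviate or miss a sample keep their records, so the full and per-protocol sets remain distinct.

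A reader might also infer that bleeding events are erased outright. Section 2.5 notifies the parent team and 2.9 passes on serious adverse events, so a bleed would presumably survive in hospital notes. What is lost is the trial's own count.

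Nor do the documents show that the primary result would be biased. Assays come after the end of the study, so nobody can withdraw in response to a known non-response. A link between withdrawal and outcome is conjecture, and a p-value crossing 0.05 is only one of several assumed patterns.

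Finally, the reference to regulatory requirements may narrow what is destroyed, and the consent form is not shown. As written, however, the phrase describes how destruction is done and states no exception. The five-year storage in 2.9 does not mention withdrawn patients either.

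**Conclusion.** The point holds as a conflict between two stated rules. Section 2.5 destroys everything on a patient who withdraws from the study, and 2.8.2 requires every allocated patient in the primary analysis. For any such patient, 2.8.2 cannot be followed, a bleed before withdrawal is lost from the count in 2.7, and a day-3 sample already drawn may go unassayed.

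The size depends on the number of study withdrawals, which the article does not state. The firm figure is 4.8% of an arm per erased patient. The bleeding, p-value and power figures rest on assumed counts or a back-solved effect and are illustrative only. The case for acting beforehand is that destruction cannot be undone and the repair is a change of wording.

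**What to change.** Change 2.5, and the consent form if it says the same, along these lines:

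- On withdrawal from the study, no further data or samples are collected. Data and samples already obtained are kept and analysed in the allocated arm, unless the patient specifically asks for their destruction.
- Where a patient does ask, and where the IRB and regulations allow, a de-identified record of arm, withdrawal date, reason and adverse events is still kept.

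In 2.8.2, state that the full analysis set includes all allocated patients and that withdrawals are reported by arm. Handle missing day-3 TXB2 with a best-case and worst-case sensitivity analysis. The article is not at fault for leaving that method to an analysis plan, but the retained records are what make it possible.

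Cost: IRB approval of the revised wording, and one more consent option to explain to patients. No extra visits, samples or assays beyond those already planned.

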### Primary outcomes

2.6

Incidence of Aspirin non-responders at day 3 (level of residual serum TXB2 associated with elevated thrombotic risk (<99.0% inhibition or TXB2 >3.1 ng/mL).

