### Setting and participants

2.2

Patients (male and female) (N = 42) with newly diagnosed ischemic stroke who are just to start aspirin therapy, and who attend stroke units of designated recruitment centers (Hamad General Hospital). We will enroll participants meeting the following inclusion criteria:

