#### Sample size

2.8.1

There are no previous studies to allow for a robust estimation of the study sample size. However, given that this is proof of concept study, we estimated that a sample size of 21 patients in each arm of the study would yield an approximate 80% power to detect 50% difference in population mean, for two-sided significance and an alpha level of 0.05.

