## Discussion

3

Our study is the third study assessing the possible effect of enteric-coated aspirin formulation on TXB2 inhibition. The first study was in 2006 by Cox et al. In their study of seventy-one healthy volunteers taking both Plain and EC aspirin in a randomized crossover design, they concluded that EC aspirin was not as effective as plain Aspirin in terms of TXB2 inhibition. The second study was in 2017 by Bhatt et al. It examined 40 diabetic patients in a randomized crossover design. Again, it concluded the inferiority of EC aspirin formulations compared to plain Aspirin (High proportion of incomplete TXB2 inhibition).

The findings from the previously mentioned trials prompted us to perform the first trial (up to the best of our knowledge), examining the level of TXB2 inhibition in stroke patients taking various formulations of Aspirin (plain vs EC aspirin). If a difference is TXB2 is found in our trial, this significant finding will invite additional clinical trials exploring the efficacy of various formulations of Aspirin measured via hard clinical outcomes such as major adverse cardiovascular events (MACE).

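### The stated 80% power belongs to a difference in mean TXB2, but the only primary outcome is a yes/no cut of TXB2, for which power is at most about 60% if the effect is a simple shift

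*Protocol article*

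**What the plan says.** - **Primary outcome (2.6).** The single primary outcome is "Incidence of Aspirin non-responders at day 3 (level of residual serum TXB2 associated with elevated thrombotic risk", with non-response defined by "<99.0% inhibition or TXB2 >3.1 ng/mL". The section describes this level as one linked to higher thrombotic risk. The only secondary outcome (2.7) is gastrointestinal bleeding, so TXB2 as a level is not a listed outcome.
- **Measurement (2.4).** Blood is taken for "estimation of the TXB2 level at baseline and on day 3, which marks the end of the study", so both values exist on a continuous scale.
- **Sample size (2.2 and 2.8.1).** "Patients (male and female) (N = 42" in total. Section 2.8.1 says that "a sample size of 21 patients in each arm of the study would yield an approximate 80% power", for a 50% difference between means, two-sided alpha 0.05. It adds that no earlier study allows a robust estimate, and it gives no SD, scale or expected non-responder rate.
- **Analysis (2.8.3).** The methods named are Wilcoxon or t tests, ANOVA of change in TXB2, correlation and linear regression. All of them treat TXB2 as a level.
- **Question (Discussion).** The trial is described as "examining the level of TXB2 inhibition in stroke patients taking various formulations of Aspirin (plain vs EC aspirin", and a difference in TXB2 is what would prompt further trials.

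**The concern.** Sections 2.8.1, 2.8.3 and the Discussion are built around the TXB2 level, while section 2.6 makes a dichotomy of that level the sole primary outcome. A reader will take the 80% as the chance that the primary analysis detects the planned effect, but it was stated for a different quantity.

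The choice also has a statistical price in many settings. A cut treats a patient just past the threshold like one with almost no inhibition, and with 21 per arm the lost information can matter. Whether it does here, and by how much, depends on how the formulation changes the TXB2 distribution, which the document does not say.

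**Working it through.** **Inputs from the document.** n = 21 per arm (2.8.1), total 42 (2.2), two-sided alpha 0.05 and power about 80% for a difference in means (2.8.1).

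**Assumptions, not in the document.** In steps 2 to 4, normal values with equal variance on the analysis scale, a pure shift between arms, and one cut. The stated definition joins a baseline-relative criterion and an absolute one, so one cut is a simplification.

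**Step 1. The plan's own figure.** The 80% cannot be checked forward without an SD, so I solve for the standardised difference d that it implies.

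- Normal approximation: d = (1.960 + 0.842) × √(2/21) = 0.865.
- t test: noncentral t with 40 df and noncentrality d × √(21/2), power 0.80, gives d = 0.886.
- If the 50% is relative to the reference mean, this corresponds to a CV of 0.50/0.886 = 0.56 to 0.50/0.865 = 0.58.

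**Step 2. Convert the shift to non-responder rates.** If p1 is the rate in one arm, the other is p2 = Φ(Φ⁻¹(p1) + d). With the cut midway between the arms, p1 = Φ(−0.443) = 0.329 and p2 = 0.671.

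**Step 3. Power for the yes/no outcome.** The approximation is Φ{[(p2 − p1)√n − 1.96√(2p̄q̄)] / √(p1q1 + p2q2)}. At the midway cut it is (0.342 × 4.583 − 1.386)/0.664 ≈ 0.27, so power is about 0.61. Exact enumeration of all 22 × 22 outcomes gives:

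| Non-responders, arm 1 v arm 2 | Fisher | Chi-square, uncorrected |
|---|---|---|
| 33% v 67% (best cut) | 47% | 60% |
| 15% v 44% | 43% | 58% |
| 10% v 35% | 37% | 51% |
| 5% v 22% | 25% | 39% |

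The uncorrected chi-square has a maximum size of 5.6%. Boschloo's test, with maximum size 4.8%, also has about 60% power at the best cut, so 60% is attainable with a valid test and 47% reflects Fisher's conservatism. On the same data the t test has 80% and the rank-sum test 78%. With d = 0.865 the best-cut figures are 58% and 45%.

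**Step 4. Patients needed.** Under this model, 80% power on the yes/no outcome at the best cut needs about 33 to 34 per arm (38 to 40 with continuity correction), against 21 planned.

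**Step 5. Sensitivity to scale.** With lognormal values, a two-fold ratio and a log-SD of 0.7, a t test on the raw scale has 80% power and on the log scale 89%. The midway cut has 70% (chi-square) or 57% (Fisher). The loss against the log-scale analysis is again about 19 points or more.

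**Step 6. Sensitivity to shape.** Suppose instead that patients form two clusters and the arms differ in the share falling in the non-responder cluster (simulated, cut midway between clusters). These cases are not calibrated to 80% and show direction only.

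| Non-responders | Separation | t test | Fisher | Chi-square |
|---|---|---|---|---|
| 20% v 60% | 2 SD | 48% | 31% | 43% |
| 20% v 60% | 3 SD | 63% | 50% | 65% |
| 20% v 60% | 4 SD | 67% | 60% | 73% |

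At 10% v 50% and 4 SD, the t test has about 74%, the rank-sum test 62% and chi-square 82%. With well-separated clusters the cut can be the better analysis.

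**The case against.** The strongest defence is that the cut is deliberate. Section 2.6 ties it to thrombotic risk, the Introduction frames the problem partly as aspirin resistance, and the Discussion reports the most recent earlier trial as a high proportion with incomplete inhibition. An incidence of non-responders is a defensible target, and the documents support both readings of the aim. That stands. It does not make the 80% apply to that target.

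It also stands that no power figure here can be a flat fact. The document gives no SD and no distribution, so a reader who infers that the cut lowers power from 80% to 47–60% goes further than the text allows. The range needs the shift model, its low end depends on choosing Fisher's test, and complete failure in a subgroup would shrink or reverse the loss.

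A reader might also infer that a null primary result could wrongly end the follow-on outcome trials. The documents do not support this. Section 2.8.3 already plans analyses of TXB2 as a level, and the Discussion ties further trials to any TXB2 difference, not to significance on the yes/no outcome.

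Finally, the absence of a named test for proportions could be left to a fuller plan. The point does not rest on that absence. It rests on the power statement in 2.8.1 and the outcome in 2.6 referring to different quantities.

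**Conclusion.** The mismatch holds without any modelling: the stated power is for a mean, and the primary outcome is a proportion.

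Its size is conditional. Taking the 80% at face value, and assuming a normal equal-variance shift with one cut, the primary outcome has at most about 60% power with an efficient test, a loss of at least 20 points. With Fisher's test it has 47%, and with uncommon non-responders it has less (39% and 25% at 5% v 22%). If the formulation effect is a subgroup of complete failures, the yes/no outcome may do as well as the continuous one or better.

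The case for a continuous primary outcome is that it matches the sample-size statement, the named analyses and the question in the Discussion, using data already collected. The dichotomy is not indefensible, but it needs its own power statement.

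**What to change.** - **2.6.** Make day-3 serum TXB2 on the log scale the primary outcome, compared between arms by ANCOVA with log baseline TXB2 as covariate and reported as a ratio of geometric means with a 95% CI.
- **2.7.** List non-responder incidence as the first secondary outcome, with a risk difference and 95% CI.
- **2.8.1.** State that the 80% refers to the continuous outcome, and give the SD and scale assumed.
- **2.8.3.** Name the ANCOVA as the primary analysis.
- **If the yes/no primary is kept.** Name a two-sample test of proportions and restate the power for assumed non-responder rates. Under the shift model that is about 60% or less with 21 per arm.

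The cost is wording in these sections and a registry update, with no extra patients, samples or assays. The downside is a headline result less directly tied to the thrombotic-risk threshold, although the non-responder rate is still reported.

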### Study design and settings

2.1

This is an open-label, two-arms, parallel, non-randomized (consecutive patients’ randomization) proof of concept, phase 4 pharmacokinetic/ pharmacodynamic study. We will recruit eligible patients from the stroke unit of designated recruitment centers (Hamad General Hospital). Patients who satisfy pre-specified inclusion criteria will be invited to participate in the study. Patients who agreed to take part will be screened, counseled, and enrolled in the study. They will be required to sign a consent form before allocation. This study was approved by the local MRC and The Institutional Review Board (IRB) (Hamad Medical Corporation, **MRC number: 01–18–156**) and registered in clinicaltrials.gov (NCT04330872) (Fig. 1).

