### Randomization, allocation concealment, and blinding

2.3

Consecutive patients meeting the eligibility criteria will be explained about the study procedures by one of the trial investigators following that that patient will be consented by designated study investigators (Supplementary materials 1. Consent form). If the patient consents to participate in our trial, then he/she will be allocated to either plain or EC aspirin arms following their admission order. Outcome assessors and data analysts are blinded to patient allocation.

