#### Statistical analysis

2.8.3

Descriptive statistics would be carried out to summarize the demographic, clinical, and laboratory characteristics of the study population. Within and between-group, changes in study parameters will be analyzed using Wilcoxon signed Rank test or Student's *t* test as appropriate. Median change of TXB2 levels from baseline will be determined by repeated measures analysis (ANOVA). Spearman correlation coefficients would be used to estimate the relationship between independent variables. Variables with *P* < .2 in univariate analyses will be entered into a multivariate model. Multivariate linear regression analysis will be used to assess the effects of covariates on thromboxane A2 levels. All analyses will be carried with StatsDirect version 2.7.9 (StatsDirect Ltd, Altrincham, Cheshire, UK).

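### Non-response is judged partly against the patient's own baseline TXB2, but no baseline-adjusted comparison of it is described in a study without random allocation

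*Protocol article*

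**What the plan says.** All references are to the protocol article.

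- **Primary outcomes (2.6).** The outcome is the incidence of aspirin non-responders at day 3, defined by a "level of residual serum TXB2 associated with elevated thrombotic risk (<99.0% inhibition or TXB2 >3.1 ng/mL"). The text does not say whether either limb alone makes a patient a non-responder or whether the limbs are alternative definitions.
- **Interventions (2.4).** Blood is taken for "estimation of the TXB2 level at baseline and on day 3, which marks the end of the study". No other TXB2 sample is mentioned, so percentage inhibition can only be relative to the patient's own baseline.
- **Study design and settings (2.1)** describes the study as "open-label, two-arms, parallel, non-randomized (consecutive patients’ randomization) proof of concept". The section on randomization (2.3) says that patients are "allocated to either plain or EC aspirin arms following their admission order".
- **Sample size (2.8.1)** plans "a sample size of 21 patients in each arm of the study".
- **Statistical analysis (2.8.3).** The one model with covariates is for a continuous level: "Multivariate linear regression analysis will be used to assess the effects of covariates on thromboxane A2 levels". Baseline TXB2 is not named as a covariate, and no adjusted comparison of the binary primary outcome is described.

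**The concern.** A percentage-inhibition criterion brings the pre-treatment value into the definition of the outcome. Two patients with the same day-3 TXB2 can be classified differently because they started from different levels. Random allocation would balance baseline in expectation, and the test's error rate would allow for chance imbalance. Allocation by admission order gives no such assurance, and no planned adjustment of the primary comparison takes its place.

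At stake is the reading of the main result. A difference in non-responder incidence, or its absence, could reflect pre-treatment TXB2 and be reported as an effect, or lack of effect, of enteric coating.

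**Working it through.** **Inputs from the protocol article:** the two-limb rule (2.6), sampling at baseline and day 3 (2.4), allocation by admission order (2.3), and 21 per arm (2.8.1). It gives no baseline TXB2, no SD and no expected non-responder rate.

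**The plan's own figure.** The 21 per arm is said to be such that it "would yield an approximate 80% power to detect 50% difference in population mean", "for two-sided significance and an alpha level of 0.05". By the normal approximation this is a standardised difference of (1.960 + 0.842) × √(2/21) = 0.865. That means a coefficient of variation (CV) near 0.5/0.865 = 0.58 if the 50% is relative to the mean. With no SD stated, the figure can be neither reproduced nor refuted. It is used below only as the arm size.

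**Step 1: the working cut-off.** Let B be baseline TXB2 and R day-3 TXB2. Inhibition below 99.0% means R > 0.01 × B. If either limb suffices, a patient is a non-responder when R > min(3.1, 0.01 × B). The limbs meet at B = 3.1/0.01 = 310 ng/mL.

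| Baseline (ng/mL) | Working cut-off (ng/mL) |
|---|---|
| 100 | 1.0 |
| 200 | 2.0 |
| 300 | 3.0 |
| 310 or more | 3.1 |

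With R = 1.5 ng/mL, a patient with baseline 100 has 98.5% inhibition and is a non-responder. A patient with baseline 300 has 99.5% inhibition and is a responder. The baseline dependence comes from the percentage limb, and the 3.1 limb caps it.

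**Step 2: what a baseline difference does when formulation has no effect.** All values here are assumptions: log-normal baseline with CV 0.5, and residual log-SD 0.8. Two models are compared:

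- *Independent:* R has median 1.5 ng/mL whatever the baseline.
- *Proportional:* R has median 0.6% of the patient's baseline.

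Simulated non-responder incidence, lower-baseline arm v higher-baseline arm:

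| Model | Median baselines | Composite | <99% limb alone | >3.1 limb alone |
|---|---|---|---|---|
| Independent | 200 v 250 | 39.0% v 31.5% | 37.9% v 29.1% | 18.2% v 18.2% |
| Independent | 200 v 300 | 39.0% v 26.7% | 37.8% v 22.8% | 18.2% v 18.2% |
| Independent | 150 v 300 | 50.3% v 26.8% | 50.0% v 22.8% | 18.2% v 18.2% |
| Independent | 400 v 600 | 21.8% v 18.9% | 14.6% v 6.8% | 18.2% v 18.2% |
| Proportional | 200 v 250 | 28.2% v 30.7% | 26.1% v 26.1% | 15.3% v 21.7% |
| Proportional | 200 v 300 | 28.2% v 34.1% | 26.2% v 26.1% | 15.3% v 27.9% |
| Proportional | 400 v 600 | 42.0% v 56.9% | 26.1% v 26.1% | 39.2% v 56.3% |

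With a baseline log-SD of 0.5 in place of CV 0.5, the proportional 200 v 300 result is about 28% v 35%.

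**Step 3: false-positive rates at 21 per arm, two-sided 0.05.** With equal baselines of 200 in the independent model, the chi-square test rejects in 5.1% and Fisher's test in 2.1%. At 200 v 300 the rates are 14.3% and 7.3%, and at 150 v 300 they are 35.1% and 22.5%. In the proportional model at 400 v 600 they are 15.2% and 8.7%.

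**Step 4: plausible size of imbalance.** With CV 0.5 the log-SD of baseline is √ln(1.25) = 0.472. The 95% limit for a chance ratio of geometric means is exp(1.96 × 0.472 × √(2/21)) = 1.33. The 200 v 250 rows (ratio 1.25) lie within it. The ratios of 1.5 and 2 would need a systematic difference as well.

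**Step 5: does adjustment help?** Unadjusted null odds ratios for the composite follow from the table:

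- 150 v 300, independent: (0.268/0.732)/(0.503/0.497) = 0.36.
- 400 v 600, proportional: (0.569/0.431)/(0.420/0.580) = 1.82.

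With log baseline TXB2 in a logistic model, the simulated null odds ratios lie between 0.90 and 1.02 under both models. This speaks to bias, not to precision with 21 per arm.

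**The case against.** The strongest case on the other side has five parts.

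1. *The rule itself is not at fault.* A reader might infer that joining the limbs by 'or' creates the baseline dependence. It does not. Any percentage-inhibition endpoint has it, and the 3.1 limit restricts it. This stands.
2. *A baseline-dependent cut-off need not bias anything.* If residual TXB2 scales with baseline, the percentage limb is the one that corrects for baseline, and the fixed 3.1 limb brings in the imbalance. This also stands. A reader might infer that the 3.1 limb alone should become the primary outcome, or that a claim should depend on it. The documents do not support that. In the proportional case at 200 v 300 that limb alone gives a gap of 27.9 − 15.3 = 12.6 points, against 34.1 − 28.2 = 5.9 for the composite.
3. *The size is unknown.* The article gives no baseline values, so the share of patients below 310 ng/mL cannot be stated, and some scenarios show little shift. This stands and limits the claim.
4. *Safeguards exist.* Patients must be about to start aspirin. Concomitant antiplatelet drugs, prostaglandin-related drugs and salicylate supplements are excluded, which makes earlier drug exposure a weak explanation for imbalance. The article also plans between-group comparisons of study parameters and analyses of TXB2 change from baseline. These lessen the concern, but none adjusts the comparison of non-response for baseline.
5. *Adjustment may be left to the analysis plan.* That is often so, and silence alone would be no finding. Here the outcome rule that brings baseline in is stated, the allocation that fails to protect it is stated, and the covariate model that is described is aimed at a different variable.

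The 'or' might also mean two alternative definitions. The cut-off formula would then not apply, but the primary outcome would not be uniquely fixed, and the wording would still need settling.

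**Conclusion.** The point holds in a limited form. If either limb suffices, it is exact algebra that the working cut-off is the lower of 3.1 ng/mL and 1% of baseline. With allocation by admission order and no baseline-adjusted comparison of non-response described, a baseline difference between arms can change the non-responder incidence when formulation has no effect.

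Size and direction are not known. In the scenarios shown, the shift runs from about 3 points in either direction to 24 points down (50.3% v 26.8%) or 15 points up (42.0% v 56.9%) in the arm with the higher baseline. All of these rest on assumed baseline medians, spread and residual levels that the documents do not supply.

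The documents do not show that the result will be biased, that any bias would favour one formulation, or that the composite is the wrong primary outcome.

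**What to change.** - **In 2.6:** keep the composite as primary, and state that either limb suffices and that inhibition is relative to the patient's own baseline sample.
- **In 2.8.3:** make the between-arm comparison of non-response a model adjusted for log baseline TXB2, for example logistic regression with arm and log baseline, penalised if events are sparse.
- **Support it** with log day-3 TXB2 compared by arm and adjusted for log baseline, and with the incidence for each limb reported separately by arm.
- **Do not** replace the primary outcome with the 3.1 limb or make a claim depend on that limb. It is the more baseline-sensitive one if residual TXB2 scales with baseline.

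Both TXB2 values are already to be collected, so only the wording of the protocol and analysis changes. The cost is one extra model term with 42 patients, and some loss of simplicity against a plain comparison of two proportions. Adjustment deals with measured baseline TXB2 only. It does not repair other differences that non-random allocation may bring.
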